#### Randomization

Participants will be randomized 1:1 using a computer-generated block size permuted randomization list (block sizes 2 and 4). The randomization will be stratified for treatment center and age (< 69 and ≥ 69 years). The age stratification is based on prior experiences with the remote monitoring platform regarding age-related digital literacy, and the distribution of cataract incidence among age deciles (mean age in the Netherlands in 2019 was 73 years [14]).

#### Study measurements

The ‘telemonitoring’ group will have a post-operative follow-up involving web-based eye exams, digital questionnaires and telephone consultations. The invitations for the web-based eye exams and questionnaires will be sent via e-mail at 4 specific time points: prior to surgery, < 1 week after the surgery, 4-6 weeks after the surgery and 3 months after surgery. Prior to surgery, visual acuity will be assessed with the participant’s current spectacles, if applicable. After surgery, the web-based eye exam will be performed without spectacles. In addition, participants will fill out triage questionnaires to identify any (alarming) symptoms.

Shortly (1-7 days) after surgery, uncorrected distance visual acuity (UDVA) will be assessed remotely, and a telephone consultation will take place if deemed necessary by the surgeon. Approximately 1 month (i.e. 4-6 weeks) after surgery, the web-based tool will assess uncorrected visual acuity (distance and near) and the residual refractive error. After performing this remote assessment at home, participants will have an in-hospital ophthalmic examination with conventional visual acuity and refraction assessments for validity and safety purposes. The observer and participant will be blinded for the web-based refraction outcome during the manifest refraction. At this in-hospital consultation, distance visual acuity will be assessed by an ETDRS chart at 4 m, both uncorrected (UDVA) and corrected (CDVA). The CDVA will be assessed twice: using both the prescriptions of the web-based and the manifest refraction. Near visual acuity will be assessed uncorrected using a Sloan ETDRS chart at 40 cm. Three months after surgery, the web-based assessment will be repeated and participants will be requested to fill out a questionnaire about their experiences with the web-based eye exam. In addition, a sample of the Dutch-speaking participants will be interviewed to further explore their perspective on remote follow-up after cataract surgery.

The ‘usual care’ group will have a post-operative follow-up adhering to the clinic’s usual practice. Typically, regular consultations will be planned within 1 week after surgery (i.e. short-term evaluation) and at approximately 4-6 weeks after surgery (i.e. long-term evaluation). The latter will include a full ophthalmic examination and refraction assessment, to assess post-operative visual outcomes and residual refractive errors. In some of the participating centres, the short-term follow-up evaluation will be a telephone consultation instead of an in-hospital consultation, or no consultation at all, depending on the standard guidelines of this clinic.

For both study groups, all adverse events and additional consultations - at other moments than the specified time points in the study flow chart - will be registered. Prior to (i.e. at baseline) and 3 months after surgery, participants of both groups will be requested to fill out questionnaires about quality of life (EQ-5D-5L [24]) and visual function (Catquest-9SF [22], NEI-VFQ-25 [23]). Three months after surgery, all participants will be requested to fill out a short custom questionnaire about expenditures related to hospital visits (such as costs for transportation and parking).

### Statistical analysis

Data will be collected and analyzed preoperative (i.e. at baseline) and at three postoperative time points. All quantitative variables will be summarized. The data will be tested for distribution, and if not normally distributed the corresponding non-parametric test will be used. For all analyses, a *P* < .05 is considered statistically significant.

Comparisons between the web-based eye exam and the conventional clinical assessments will be analysed according to the Bland-Altman methodology [32]. We will compare assessments of distance visual acuity, near visual acuity and refractive error. Furthermore, we will analyse independent associations between clinical characteristics and agreement between the web-based exam and the conventional reference tests. Safety of the remote follow-up will be evaluated by comparing the occurrence of adverse events in both study groups. The cost-effectiveness will be assessed by QALYs, total costs, and the probability of adverse events and additional clinical examinations.

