#### Validity of the web-based eye exam

Validity of the web-based eye exam (developed by Easee B.V.) will be assessed by comparing the web-based outcomes to the clinical findings at the visit scheduled 4-6 weeks after surgery. Our main objective will be to determine if the corrected distance visual acuity (CDVA) achieved with the refraction resulting from the remotely performed web-based refraction assessment is non-inferior to the achieved CDVA with the prescription of the in-hospital manifest refraction. A mean difference between the two scores up to 0.10 logMAR (one ETDRS line) will be considered clinically acceptable (i.e. non-inferior). In addition, we will assess uncorrected distance visual acuity (UDVA) and compare the outcomes of the web-based vs. the in-hospital assessment. Furthermore, we will evaluate the accuracy of the web-based exam for determining refractive error and uncorrected near visual acuity, by comparing these outcomes to the conventional in-hospital assessments. The repeatability of the web-based refractive assessment will be determined by comparing the outcomes 4-6 weeks after surgery to the outcomes 3 months after surgery (on the condition that post-operative complications resulting in a change of visual function are absent).

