#### Patients’ perspective

Firstly, we will determine if remotely self-assessing vision influences patient-reported outcome measures of visual function (Catquest-9SF and NEI-VFQ-25 questionnaires [22, 23]) and quality of life (EQ-5D-5L questionnaire [24]), by comparing the outcomes between both randomization groups.

Secondly, we will evaluate the user experiences with the web-based tool by a custom quantitative questionnaire, distributed amongst the participants of the telemonitoring group at the end of the study. This questionnaire is based on the theoretical Technology Acceptance Model; a commonly used model to evaluate and incorporate user experiences in the development process of technology. Since its introduction by Davis in 1989 [25], the model has been extended by multiple research teams, including for utilization in health care settings [26–28]. We used the extended models as a reference framework and developed a study-specific questionnaire in cooperation with the University of Twente, the Netherlands (Additional file 1). Lastly, the quantitative results are enriched with in-depth qualitative interviews (Additional file 2). Dutch-speaking participants of the telemonitoring group will be invited to report on their experiences with the web-based eye exam. Interviews will be conducted by researchers experienced in qualitative interview studies, until data saturation is reached (i.e. when no longer new insights are gained).

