### Study population and sample size calculation

Patients planned for bilateral cataract surgery without visual acuity influencing comorbidities are eligible for study participation. The surgical procedures can be performed on the same day (i.e. immediate sequential) or on two different days. Exclusion criteria are: cataract surgeries combined with other procedures (including keratoplasty, vitrectomy, glaucoma filter implants), presence of ocular comorbidities that negatively influence post-operative visual acuity (such as amblyopia, age-related macular degeneration, diabetic retinopathy, glaucoma or uveitis), insufficient command of the Dutch, German or English language, no access to a smartphone and computer/tablet, and inability to successfully perform the demo version of the web-based eye exam.

The sample size calculation is based on determining the validity of the web-based eye exam since calculations based on cost-effectiveness and safety were not feasible. We aim to assess whether the corrected distance visual acuity obtained with the web-based refraction is not significantly worse than the visual acuity obtained with the manifest refraction. We assume no difference between the measurements and consider a difference up to 0.10 logMAR to be non-inferior. With a standard deviation of 0.30 logMAR (a commonly used SD in power calculations on visual acuity [29–31]), an α of 0.05, a power of 90, 20% loss to follow-up and using a one-sided, one sample t-test, 94 eyes are then required in the telemonitoring group (so 47 participants, as all measurements will be performed bilaterally). This results in a total study population of 94 participants (188 eyes) for both study groups.

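### The general switch to non-parametric tests does not exempt the main non-inferiority comparison, whose 0.10 logMAR margin is set on a mean

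*Protocol article*

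**What the plan says.** Three parts of the protocol article bear on the main comparison.

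- **Validity of the web-based eye exam.** The main objective is non-inferiority of the CDVA reached with the web-based refraction to the CDVA reached with the manifest refraction. The criterion is worded as "A mean difference between the two scores up to 0.10 logMAR".
- **Study population and sample size calculation.** The same margin is used: "We assume no difference between the measurements and consider a difference up to 0.10 logMAR to be non-inferior". The inputs are "With a standard deviation of 0.30 logMAR" and "an α of 0.05, a power of 90, 20% loss to follow-up", with a one-sided one-sample t-test. The result is 94 eyes (47 participants) in the telemonitoring group.
- **Statistical analysis.** The general rule is "The data will be tested for distribution, and if not normally distributed the corresponding non-parametric test will be used". No outcome is exempted. The section then assigns comparisons of the web-based exam with clinical assessments to Bland-Altman methodology. It does not return to the test against the margin.

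**The concern.** The non-parametric counterpart of a one-sample t-test is the Wilcoxon signed-rank test. Applied to the CDVA difference minus 0.10, it tests the pseudo-median. That equals the mean only if the differences are symmetric. Under the rule, a preliminary test on the data therefore decides which quantity is held to the 0.10 margin.

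The direction of the likely asymmetry matters. Manifest refraction is the reference, so a poor web-based refraction can cost many letters but can hardly gain many. The exam is also done unsupervised at home. A cluster of differences near zero with a tail of large losses is plausible. A rank test gives that tail little weight, although these eyes are what raises the mean loss. At stake is the trial's main claim: the analysis could declare non-inferiority when the mean loss fails the plan's own criterion.

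**Working it through.** **1. The plan's own figure.** Inputs from the sample size section: SD 0.30, margin 0.10, true difference 0, one-sided α 0.05, power 90%, loss 20%.

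n = (SD × (z₀.₉₅ + z₀.₉₀) / margin)² = (0.30 × 2.9264 / 0.10)² = 77.07, so 78 eyes (79 by the noncentral t, power 0.902).

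78 × 1.2 = 93.6, so 94 eyes. The stated figure is reproduced, and it is a size for a test of a mean. With 20% lost, 94 × 0.8 = 75 eyes remain; the t-test then has power 0.888.

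**2. The two hypotheses.** With d = CDVA by web-based minus CDVA by manifest refraction (logMAR, positive = worse):

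- t-test: H₀ is mean(d) ≥ 0.10.
- Signed-rank: H₀ is pseudo-median(d) ≥ 0.10.

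Under right skew the centre that the rank test sees lies below the mean. For a shifted gamma with mean 0.10, SD 0.30 and skewness 2, the ordinary median is 0.008.

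**3. Error at the margin.** Assumptions: 75 independent eyes, Shapiro-Wilk at 0.05 as the distribution test (the article names none), shifted gamma, true mean exactly 0.10, SD 0.30, 5,000 trials per row. Nominal error is 5%.

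| Skewness (assumed) | Normality rejected | Switching rule | t-test |
|---|---|---|---|
| 0 (normal) | 5% | 5.1% | 5.0% |
| 0.5 | 32% | 9.0% | 5.9% |
| 1 | 88% | 18.2% | 6.4% |
| 1.5 | >99% | 28.3% | 6.6% |
| 2 | 100% | 41.4% | 7.6% |

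With a true mean of 0.13 and skewness 2, the rule passes in 15.2% of trials and the t-test in 1.4%.

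**4. A cluster with a tail.** Assumptions: 75 independent eyes; most differences N(0, 0.06), the rest N(centre, 0.15), rounded to 0.02; 3,000 trials per row. True mean = tail share × tail centre.

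| Tail share and centre (assumed) | True mean | Switching rule | t-test |
|---|---|---|---|
| 15% at 0.70 | 0.105 | 93% | 5.7% |
| 20% at 0.55 | 0.110 | 63% | 4.2% |
| 20% at 0.60 | 0.120 | 63% | 2.2% |
| 25% at 0.50 | 0.125 | 27% | 0.8% |
| 30% at 0.35 | 0.105 | 22% | 4.7% |
| 40% at 0.27 | 0.108 | 11% | 2.7% |
| 50% at 0.22 | 0.110 | 5.6% | 1.8% |
| 40% at 0.30 | 0.120 | 4.2% | 0.8% |
| 10% at 0.30 | 0.030 | >99% | 99% |

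In every row but the last, the true mean is beyond the margin, so a pass is wrong. In the last row a pass is right. Normality was rejected in 98% of trials or more in every row. Monte Carlo error and the treatment of ties can move single entries by a few points.

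**5. Costs, if the rule reaches them.** With 47 per arm, equal true mean costs and lognormal data, assumed coefficients of variation of 0.5 and 1.0 make the Mann-Whitney test reject in 36.5% of trials and the Welch t-test in 6.5%. With equal coefficients (0.5 in both arms) the figures are 4.2% and 4.4%.

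**The case against.** The best defence is that specific statements override a general sentence. The margin is a mean, the sizing names a t-test, and Bland-Altman, which centres on the mean difference, is assigned to the web-versus-clinic comparisons. A reader may take these to govern the main objective. This stands as a possible reading, so the defect may be one of wording rather than intent. It does not remove the problem: Bland-Altman describes agreement, and nothing in the article takes the test against the margin out of the switch.

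The second objection is that the size depends on the assumed tail. This stands. The 93% row needs 15% of eyes to lose about seven lines; with more frequent but milder losses the false claims fall to about 4–5%. Nor is rejection of normality certain, since the article gives no distribution for these differences.

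Three stronger readings are tempting, but the document does not support them.

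- **Every analysis moves to rank tests.** The phrase about all analyses governs the P threshold, not the switch.
- **The cost and QALY comparison becomes a rank test.** The cost-effectiveness objective already fixes the ICER in euros per QALY, and no test for costs is named. The rule's reach to costs is an inference.
- **The plan leaves out baseline scores and stratification factors.** The article says the questionnaires are analysed "by comparing the outcomes between both randomization groups" and names no model, adjusted or not. That detail is commonly left to a full protocol or analysis plan, so its absence is no fault.

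**Conclusion.** The point holds for the main non-inferiority comparison, with medium confidence. As written, the general rule can replace the test of the mean by a test of the pseudo-median, in conflict with the margin and the sizing. If the CDVA differences are right-skewed, the error runs towards a false claim of non-inferiority: 9% to 41% at the exact margin for skewness 0.5 to 2, and about 4–5% to 93% for tailed mixtures with true means of 0.105 to 0.125. The t-test gives about 6–8% and 1–6% respectively. If the differences are symmetric, or the true mean is well inside the margin, the switch causes no false claim of this kind.

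Skewness, tail shapes and the choice of Shapiro-Wilk are assumptions, and eyes were simulated as independent. The figures show direction and possible range; they do not predict this trial's error rate. For costs the concern is only conditional.

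**What to change.** Add to the Statistical analysis section that the main analysis is the mean CDVA difference (web-based minus manifest) with a one-sided 95% upper confidence bound compared with 0.10 logMAR, whatever the distribution test shows. Compute the bound by a participant-level bootstrap or a cluster-robust standard error, because both eyes of a participant are measured. Report the signed-rank test as a sensitivity analysis only.

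If the general rule is meant to cover costs and QALYs, exempt them as well and compare arithmetic means with bootstrap intervals, since the ICER rests on means.

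The cost is a change of wording. No new data, visits or participants are needed.

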## Discussion

This is the first study to investigate remote follow-up after cataract surgery including refractive assessments. We believe that remote follow-up fits in the current trends of digitization of health care, and that it can be a promising avenue to tackle the increasing demands of cataract care. The studied population, i.e. cataract patients, is particularly interesting due to the high volume of procedures and low risks. We are aiming to provide a clear overview on validity, safety, cost aspects, and patients’ perspectives regarding remote follow-up after cataract surgery. After completion of the present study, the web-based eye exam test flow will be improved and an iteration in algorithm development will take place, focusing on additional training, recalibrating, and a machine learning approach to better control user-behavior and -environment. We anticipate to amend the current trial with a telemonitoring-only approach to further explore the performance and deliver fine granular data on the (cost-)effectiveness of the updated web-based tool.

## Data Availability

Data sharing is not applicable to this article as it does not contain any data.

## Abbreviations

CORE-RCT: Cataract Online Refraction Evaluation - a Randomized Controlled Trial
CDVA: Corrected distance visual acuity
UDVA: Uncorrected distance visual acuity
QALY: Quality-adjusted life years
